#### 2.4.2. Control Group (TAU)

The TAU provided to patients in the control group of this study is based primarily on the prescription of drugs adjusted to the symptomatic profile of each patient, with complementary advice on aerobic exercise and pain neuroscience education adapted to the physical capacities of the patients. Patients of the control group will be placed on a waiting list so that at the end of the RCT they can benefit from the NAT-FM treatment. 

### 2.5. Study Measures

The participants of the intervention group (TAU+NAT-FM) and the control group (TAU) will complete the instruments described below. Assessment will be organized considering the timings (CSA+EMA) that were established from the results of the proof of concept study [41]. Table 3 shows the measurement scheme and timings for the NAT-FM treatment protocol.

#### 2.5.1. Classical Structural Assessment (CSA)

The CSA will measure general information, clinical characteristics and screening, primary outcomes, secondary outcomes, and additional secondary outcomes. These instruments will be applied to patients in both the control group (TAU) and intervention group (TAU+NAT-FM).

##### General Information Measures

The Socio-demographic and clinical questionnaire will be used to obtain general and clinical patient data (age, educational level, socioeconomic status, marital status, ethnic group, personal medical history, years of FM diagnosis, comorbid medical conditions, etc.).

##### Measures of Clinical Features and Screening

The Structured Clinical Interview for DSM Axis I Disorders (SCID-I) [43] will be used for the diagnosis of mood disorders. It is based on the research version of SCID-I and the DSM-IV criteria. 

##### Primary Outcome Measure 

The Revised Fibromyalgia Impact Questionnaire (FIQR) comprises three dimensions: physical dysfunction (scores from 0 to 30), overall impact (scores from 0 to 20), and intensity of the symptoms (scores from 0 to 50), which are used to measure the impact generated by FM during the last week. It consists of 21 items, which are answered on a numerical rating scale of 11 points (from 0 to 10). Total scores can range from 0 to 100, with higher scores reflecting greater deterioration. The Spanish version has an adequate internal consistency (*α* = 0.93) and acceptable test-retest reliability (*r* = 0.84) [44].

##### Secondary Outcome Measures

The Positive and Negative Affect Schedule (PANAS) is used to evaluate positive and negative affects. It consists of two dimensions (positive affect and negative affect) of 10 items, each answered on a 5-point Likert scale. Total scores of each scale range from 10 to 50, where higher scores indicate a greater presence of the specific affectivity. The Spanish version has an adequate internal consistency for the positive affect (*α* = 0.92) and for the negative affect (*α* = 0.88) [45].

The Cognitive Emotion Regulation Questionnaire (CERQ) is used to assess individual differences in the cognitive regulation of emotions. The instrument measures nine 2-item dimensions (self-blame, blaming others, acceptance, refocusing on planning, positive refocusing, rumination, positive reappraisal, putting into perspective, and catastrophising). This study will use the short 18-item version. Responses are given on a 5-point Likert scale ranging from 1 (almost never) to 5 (almost always). Total scores for each dimension range from 2 to 10, with the highest scores indicating the specific cognitive strategy most used. The Spanish version has an adequate internal consistency (*α* = 0.77 to 0.93) and acceptable test-retest reliability (*r* = 0.60 to 0.85) for the subscales [46].

The Personal Perceived Competence Scale (PPCS) is used to measure perceived competence. It consists of eight items that are answered on a 6-point Likert scale. Total scores of each scale rangefrom 8 to 48, with higher scores indicating greater perceived competence. The Spanish version has an adequate internal consistency (*α* = 0.83) [47].

The Rosenberg Self-Esteem Scale (RSES) is used to measure self-esteem. It consists of 10 items that are answered on a 4-point Likert scale. Total scores of each scale range from 10 to 40, where higher scores indicate higher self-esteem. The Spanish version has an adequate internal consistency (*α* = 0.87) and acceptable test-retest reliability (*r* = 0.72 to 0.74) [48].

The Pain Catastrophizing Scale (PCS) is used to evaluate catastrophic thoughts associated with pain. It consists of three dimensions (rumination, magnification, and helplessness) of 13 items in total, which are answered on a 5-point Likert scale. Total scores on each scale range from 0 to 52, with higher scores indicating more catastrophising. The Spanish version has an adequate internal consistency (*α* = 0.79) and acceptable test-retest reliability (*r* = 0.84) [49].

The Perceived Stress Scale (PSS) is used to evaluate the stress perceived by people during the previous month. This study will use a 4-item version with a 5-point Likert type response format. Total scores range from 0 to 16, with higher scores indicating greater perceived stress. The Spanish version has an acceptable internal consistency (*α* = 0.77) [50].

##### Additional Secondary Outcomes Measures

The Hospital Anxiety and Depression Scale (HADS) is used to quantify the severity of anxiety and depression symptoms. It consists of two dimensions (anxiety and depression) of seven items, each responding on a 4-point Likert scale. Total scores of each scale (HADS-A and HADS-D) range from 0 to 21, where higher scores indicate greater severity of symptoms. The Spanish version has an adequate internal consistency for anxiety (*α* = 0.83) and for depression (*α* = 0.87) [51,52].

The Psychological Inflexibility in Pain Scale (PIPS) is used to assess psychological inflexibility in patients with pain. It consists of two dimensions (avoidance and cognitive fusion with pain) of 12 items, which are answered on a 7-point Likert scale. Total scores of each scale range from 12 to 84, with higher scores indicating greater psychological inflexibility. The Spanish version has an adequate internal consistency (*α* = 0.90) and test-retest reliability (*r* = 0.97) [53].

The Tampa Scale for Kinesiophobia (TSK-11) is used to assess fear of pain and movement. It consists of 11 items, which are answered on a 4-point Likert scale. Total scores of each scale range from 11 to 44, where higher scores indicate a greater fear of pain and movement. The Spanish version has an adequate internal consistency (*α* = 0.79) [54].

The physical function of the 36-Item Short Form Survey (SF-36) will be used to assess the physical function typically affected in patients with chronic pain. This dimension comprises a total of 10 items, which are answered on a Likert scale of 3 points. Total scores on each scale range from 0 to 100, with higher scores indicating better physical function. The dimensions have shown optimal internal consistency (*α* = 0.94) [55].

The UKK Walk Test (UKK) [56] is used to assess people’s physical fitness, endurance, and cardio-respiratory capacity (maximum VO^2^). The test is performed in a straight line with no difference in height between the two extremes. In this study, the distance from the beginning to the end of the route will be adapted from 2 km (original version) to 1 km, given the specific characteristics of the population of this study. In addition, we will use Polar Advantage heart rate monitors with their respective software to mark the times and obtain the average heart rate of the patients during the route. 

The Adverse effects Assessment Checklist [57] is an ad hoc measure to check for potential adverse events (e.g., headaches, dizziness, physical injuries) across the interventions and follow-up.

The Patient Global Impression of Change (PGIC) [58] and Pain Specific Impression of Change (PSIC) [57] are self-reported measures frequently used as indicators of meaningful change in treatments for chronic pain. Responses are given on a 7-point Likert scale ranging from 1 (much better) to 5 (much worse). The PGIC is one item that refers to the perception of global improvement, whereas the PSIC asks about the impression of change in more specific domains (physical and social functioning, work-related activities, mood, and pain). These scales will be completed by the participants assigned to the treatment (NAT-FM+TAU) group.

#### 2.5.2. Ecological Momentary Assessment (EMA)

EMA is used to assess: (a) the specific short-term impact of each activity and (b) the transfer of the treatment effects to everyday life. Measurements during the sessions (intrasession assessment) will be taken before and after each activity in nature using an online form. Measurements of the daily records between sessions (intersession assessment) will be carried out through an app, in which patients will have to respond six times a day (twice in the morning, twice in the afternoon, and twice at night). Intersession instruments will be applied to patients in both the control group (TAU) and intervention group (TAU+NAT-FM). However, intrasession instruments will only be applied to patients in the intervention group (TAU+NAT-FM).

##### Other Secondary Outcome Measurements

The Self-Assessment Manikin (SAM) [59] is used to assess the affective state of people. It consists of three blocks of diagrammed pictograms in a continuous line, representing the following three dimensions of the affective response: valence, arousal, and dominance. Each scale has a 9-point Likert response format. The total scores on each scale range from 1 to 9. Higher scores on valence indicate greater positive mood; higher scores on arousal indicate greater activation and alertness; whilst for dominance a higher score indicates greater perception of control and personal confidence. These three dimensions of the affective response were evaluated both in intrasession assessment and in intersession assessment.

Single-item questionnaires: For the assessments of the variables fatigue, pain, and sleep quality, the three items of the Visual Analog Scale (VAS) of the FIQR were selected. For stress and self-efficacy, ad hoc questions were designed with a single item, rated on a scale from 0 to 10, in a VAS format. Higher scores indicate greater perceived fatigue, pain, sleep quality, stress, and self-efficacy. The variables fatigue, pain, and sleep quality were evaluated by intersession assessment, whereas the variables energy, pain, stress, and self-efficacy were evaluated by intrasession assessment.

### 2.6. Statistical Analysis

Data analyses will be conducted by means of the statistical program SPSS v25 and MPlus 7.0. Initially, descriptive statistics will be calculated for all measures of the study (general, clinical characteristics/screening, and primary/secondary/additional secondary outcomes). Subsequently, multivariate analyses will be conducted to define the effect size of the intervention at the different assessment periods: CSA (pre, during, post, and follow-up) and EMA (during). Continuous variables will be analysed using the Kolmogorov–Smirnov test to assess normal distribution and the Levene test for equal variances. First, we will use the Student’s t-test to examine the baseline between-group differences in sociodemographic and clinical characteristics. The primary between-group analysis to assess the effect of treatment will be conducted on an intention-to-treat (ITT) basis with the FIQR total score as a continuous variable and assuming data missing at random. This involves using 2 × 4 mixed-effects ANOVA with the group (TAU+NAT-FM vs. TAU) as the between-groups factor and phase (pre, post, follow-up+6, follow-up+9) as the within-subjects factor. Corrected *ηp*^2^ (partial eta-square) will be estimated for the full model (group and phase main effects and group x phase interaction). We will also report the effect size (Cohen’s *d*) for each pairwise comparison, using the pooled baseline SD to weight the differences in the pre-post means and to correct for the population estimate. Separate models will be estimated for each of the secondary outcomes using the same analytical strategy. 

In addition, to assess the clinical significance of the improvement in the primary outcome (FIQR), we will classify participants into two categories (responders vs. non-responders to treatment), using the following criterion: ≥20% reduction in the pre–post FIQR total scores [60]. This classification will be used to compute the number needed to treat (NNT) in NAT-FM compared with TAU. Finally, we will examine whether the effect of NAT-FM on the primary outcome at post and at the 6 and 9-month follow-ups is mediated/moderated through pre–post changes in secondary measures and personal factor variables (age, years from diagnosis, severity), using a structural equation model. According to the proposal of Luciano et al. [60], change scores before and after NAT-FM treatment will be calculated for these variables, as well as change scores before follow-up for the outcome variables. The analysis of temporality will increase the possibility of drawing conclusions about causality relationships. In this process, the data of the patients of the treatment with the greatest participation in the intervention will be analysed, defining participation as a minimum of 75% attendance of the sessions (per protocol analysis). The Benjamini–Hochberg correction for multiple comparisons will be applied; a procedure to detect false findings designed to overcome the limitations of other common procedures [61].

Complementary analyses will be conducted. Firstly, EMA intrasession measurements obtained from the NAT-FM treatment group will be subjected to a 2 (pre vs. post) × 6 (type of activity) mixed-effects ANOVA for pain, fatigue, self-efficacy, stress, and affect in order to assess the short-term impact of the planned activities. Secondly, EMA between-session measurements obtained from both arms of the study will be analysed both on a time-domain (single regression linear model for each dependent variable) and a frequency-domain basis (spectral analysis for each dependent variable) in order to assess transfer of the treatment effects to daily life.

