## Abstract

The study protocol of a prospective and randomized controlled trial for the assessment of the efficacy of nature activity therapy for people with Fibromyalgia (NAT-FM) is described. The primary outcome is the mean change from baseline in the Revised Fibromyalgia Impact Questionnaire (FIQR) score at post-treatment (12 weeks) and at 9 months of follow-up, and secondary outcomes are changes in the positive affect, negative affect, pain, fatigue, self-efficacy, catastrophising, and emotional regulation. A total of 160 patients with fibromyalgia will be divided into two arms: treatment-as-usual (TAU) and NAT-FM+TAU. Pre, during, post, +6, and +9 months assessments will be carried out, as well as an ecological momentary assessment (EMA) of intrasession and intersessions. Results will be subjected to a mixed group (NAT-FM+TAU vs. TAU) × phase (pre, post, +6 months, +9 months) general linear model. EMA intrasession measurements will be subjected to a 2 (pre vs. post) × 5 (type of activity) mixed-effects ANOVA. EMA between-session measurements obtained from both arms of the study will be analysed on both a time-domain and frequency-domain basis. Effect sizes and number needed to treat (NNT) will be computed. A mediation/moderation analysis will be conducted.

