### 2.2. Participants

A total of 160 patients with FM will be recruited from the Central Sensitivity Syndromes Unit (CSSU) at the Vall d’Hebron University Hospital (Barcelona, Spain). The sample size was established using IBM SPSS SamplePower 3.0 (IBM, Chicago, IL, USA), considering the results of a meta-analysis of therapies in nature [21], which reported an average effect size of *g* = 0.50, regarding clinical variables. With the anticipation of a 20% dropout and setting alpha = 0.05 and power 1-b = 0.80, the estimated sample size is *n* = 80 participants per condition. The sample size in each of the arms and the treatment follow-up period were estimated in such a way that they will be sufficiently representative to capture important results.

Patients visited consecutively by the physical therapist of the CSSU from November to December 2020 who met the selection criteria will be recruited. The inclusion criteria will be: (a) adults ≥18 years old, (b) to meet the 2010–2011 ACR diagnostic criteria for FM [1,37,38], and (c) to be able to understand and agree to participate in the study. The exclusion criteria will be: (a) participating in concurrent or past RCTs (previous year) and (b) exhibiting comorbidity with severe mental disorders (e.g., psychosis) or neurodegenerative diseases (e.g., Alzheimer’s) that would limit the ability of the patient to participate in the RCT.

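### The primary model treats pre-treatment FIQR as an outcome level with no baseline adjustment: valid, but less precise than an adjusted contrast, and for one change contrast the 80% power depends on an unstated correlation

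*Protocol article*

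**What the plan says.** Section 2.6 specifies the primary between-group analysis as an intention-to-treat 2 × 4 mixed-effects ANOVA of the FIQR total score, with data assumed missing at random. Group is the between factor, and "phase (pre, post, follow-up+6, follow-up+9) as the within-subjects factor". The effects listed are "group and phase main effects and group x phase interaction". Neither a baseline covariate nor an equal-baseline constraint is mentioned, and the Abstract repeats the model with the same four phases. Secondary outcomes follow the same strategy.

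On the outcome, the Abstract says: "The primary outcome is the mean change from baseline in the Revised Fibromyalgia Impact Questionnaire (FIQR) score", assessed at 12 weeks and at 9 months.

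On the sample size, section 2.2 relies on a meta-analysis that "reported an average effect size of *g* = 0.50, regarding clinical variables". It then proceeds "With the anticipation of a 20% dropout and setting alpha = 0.05 and power 1-b = 0.80", and concludes that "the estimated sample size is *n* = 80 participants per condition". No correlation between baseline and follow-up enters. Table 3 shows FIQR collected at pre as well as at the later visits.

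**The concern.** In a randomised trial the two arms have the same expected FIQR before treatment. A model that gives each arm its own baseline mean estimates a difference already known to be zero in expectation, and it pays for that in precision. Every contrast between pre and a later phase then carries the full noise of the raw change score.

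Two things are at stake. First, the treatment effect at 12 weeks and at 9 months will have a wider confidence interval than the collected data allow. Second, the trial was sized as a comparison of two means at one time, whereas the effect defined in the Abstract is a difference in change. The two have the same variance only at one particular correlation, so whether the 80% carries over to a single change contrast depends on a quantity the article does not give.

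**Working it through.** **Inputs.** From section 2.2: effect 0.50, alpha 0.05, power 0.80, dropout 20%, 80 per arm. From section 2.6: pre as a level of phase, no baseline covariate. From section 2.5.1: FIQR test-retest reliability 0.84, the only FIQR correlation in the article. Assumptions: two-sided test, effect expressed in raw-score SD units (SD = 1), equal variances over time, and rho from 0.3 to 0.84.

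**Step 1: reproduce the stated size.** A two-sample t-test at d = 0.50 with 64 per arm has power 0.801 (63 per arm gives 0.795). Allowing for dropout, 64 / 0.80 = 80 per arm. The stated figure reproduces as a comparison of two independent means, with no pre–post correlation used.

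**Step 2: variance of the two contrasts.** Per patient, in SD² units:
- raw change score: 2(1 − rho)
- baseline-adjusted follow-up score: 1 − rho²

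The ratio of standard errors, adjusted to change, is sqrt[(1 − rho²) / (2(1 − rho))] = sqrt[(1 + rho)/2]. This is below 1 for every rho below 1.

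**Step 3: power with 64 evaluable per arm.** The standardised effect is 0.50/sqrt(2(1 − rho)) for change (126 df) and 0.50/sqrt(1 − rho²) for the adjusted contrast (125 df). Power comes from the noncentral t distribution with noncentrality equal to the standardised effect × sqrt(64/2).

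| rho | Change: effect | Change: power | Adjusted: effect | Adjusted: power | SE lower by |
|---|---|---|---|---|---|
| 0.3 | 0.423 | 66% | 0.524 | 84% | 19% |
| 0.4 | 0.456 | 73% | 0.546 | 86% | 16% |
| 0.5 | 0.500 | 80% | 0.577 | 90% | 13% |
| 0.6 | 0.559 | 88% | 0.625 | 94% | 11% |
| 0.7 | 0.645 | 95% | 0.700 | 98% | 8% |
| 0.84 | 0.884 | >99% | 0.922 | >99% | 4% |

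**Step 4: where the 80% is reached.** With 64 per arm the single change contrast reaches 80% at rho = 0.498. If all 80 per arm contribute, it does so at rho = 0.37. The adjusted contrast with 64 per arm is already at 80.5% at rho = 0.1.

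**Step 5: other readings of the planned test.** The group × phase interaction has 3 df. Under compound symmetry with 64 per arm, it reaches 80% at rho = 0.455 if the 0.50 effect is sustained, and at 0.615 if it fades (0.50, 0.35, 0.25, an assumed profile). A contrast of the mean of the three later phases against pre reaches it at 0.247.

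**The case against.** The strongest reply is that nothing in the plan is wrong. The outcome is defined as change from baseline, and a pre-referenced contrast estimates exactly that. Under randomisation it is unbiased, and simulated false-positive rates for both analyses were 4–5%. This stands.

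Several stronger readings are tempting, and the article does not support them.

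- *The pairing is wasted.* It is not. A change score uses it, and at rho 0.6 has 88% power against 80% for the unpaired comparison behind the sample size. The loss is only relative to adjustment.
- *The trial is underpowered whenever rho is below 0.5.* That threshold belongs to one pre-to-one-follow-up contrast with exactly 64 per arm. It moves to 0.37 with 80 per arm, and to 0.455 or 0.615 for the 3-df interaction, depending on the effect profile. Because the analysis is intention-to-treat under missing at random, patients with partial data can contribute, so 64 is the cautious end. The article also does not say which SD standardises the 0.50.
- *The 9-month contrast falls short.* A lower correlation over a longer interval is plausible, but no figure is given. The test-retest value of 0.84 is a reliability coefficient and plausibly an upper bound; there both analyses exceed 99%.
- *Chance baseline imbalance biases the result.* That variation is already in the change-score standard error. Counting it again as bias would count the same loss twice.
- *The group main effect, which averages in pre, is the efficacy test.* Section 2.6 lists it among the effects for which partial eta-squared is estimated, but never names it as the test of efficacy.

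It can also be said that covariate adjustment is often left to the analysis plan. Here, though, section 2.6 states the factors, the four phase levels and the effects of the primary model, so the choice is made on the page.

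**Conclusion.** This is an avoidable loss of efficiency in the stated primary model. It is not a bias, and it is not an error in the sample-size arithmetic. The baseline-adjusted contrast has a standard error lower by 19%, 13%, 8% and 4% at rho 0.3, 0.5, 0.7 and 0.84. The gain in power is large at low correlation (66% to 84% at 0.3) and negligible at high correlation.

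The size of the loss rests on an assumed rho, an effect of 0.50 in raw-SD units, equal variances and 64 evaluable per arm. The direction does not depend on rho, provided it is below 1. A shortfall below 80% is a possibility for single change contrasts and is not demonstrated. The change is worth making because it removes that dependence at almost no cost.

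**What to change.** In section 2.6, take one of two forms:

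1. Make FIQR at post, +6 and +9 months the responses, with baseline FIQR and its interaction with phase as covariates.
2. Keep pre as a response, but constrain the two arms to a common baseline mean. This form also retains patients who have only a baseline score.

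Under either form, report the adjusted between-arm difference at 12 weeks and at 9 months as the treatment effect. Use the same model for the secondary outcomes measured at pre.

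In section 2.2, state that the 80% power rests on a two-sample comparison of means at an effect of 0.50. The adjusted contrast meets it from rho of about 0.1 upwards.

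The cost is a change of wording and an extra term or constraint in the model. FIQR is already collected before treatment in both arms, so no patients, visits or data are added.

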This paper describes the design characteristics of the NAT-FM treatment in comparison with a treatment-as-usual (TAU). The objectives of the RCT are the following: (a) to analyse the efficacy of the NAT-FM program as an add-on to TAU in improving the functional status (primary outcome) of FM patients; (b) to compare the efficacy of NAT-FM treatment with respect to TAU in improving affectivity, emotional regulation, perceived competence, self-esteem, self-efficacy, anxiety, depression, and other secondary outcomes; and (c) to identify factors that may act as mediators or moderators of the efficacy of NAT-FM treatment (age, years of evolution, psychological inflexibility, etc.). 

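### The moderator analysis for objective (c) is set in NAT-FM attenders on change scores with no stated TAU comparison, so it shows prognosis and, for severity, regression to the mean, not moderation of efficacy

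*Protocol article*

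**What the plan says.** The third objective, in the Introduction, is "to identify factors that may act as mediators or moderators of the efficacy of NAT-FM treatment". Objectives (a) and (b) judge efficacy as an add-on to, or in comparison with, TAU.

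Section 2.6 gives mediation and moderation a single analysis. The question is whether the effect of NAT-FM on FIQR at post, 6 and 9 months "is mediated/moderated through pre–post changes in secondary measures and personal factor variables (age, years from diagnosis, severity), using a structural equation model". Three details are then fixed:

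- **Scale:** "change scores before and after NAT-FM treatment will be calculated for these variables, as well as change scores before follow-up for the outcome variables".
- **Analysis set:** "In this process, the data of the patients of the treatment with the greatest participation in the intervention will be analysed".
- **Threshold:** "defining participation as a minimum of 75% attendance of the sessions (per protocol analysis", which closes the sentence.

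No arm-by-factor term is stated for this step, and severity is not tied to a measure. Under section 2.4.2, TAU patients wait for NAT-FM until the trial ends, so they have no sessions to attend during it. Benjamini–Hochberg is to be applied to multiple comparisons.

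**The concern.** A moderator of efficacy is a baseline factor across which the NAT-FM minus TAU difference varies. The matching null hypothesis is that this difference is constant over the factor.

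In treated attenders alone, the path from a factor to FIQR change has another null: that the factor does not predict change in treated patients. That null is false for any factor that predicts the natural course of the disease. If severity is baseline FIQR, it is also false through regression to the mean, since high scores tend to fall on retest whether or not treatment works better in those patients. Without TAU patients nothing separates the three sources, and a larger sample does not help.

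At stake is the answer to objective (c). The trial could report that NAT-FM works better in more severe patients, or depends on age or years from diagnosis, when TAU patients would show the same pattern. The intention-to-treat primary analysis is not affected.

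**Working it through.** **Inputs from the protocol article**

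- 80 per arm, g = 0.50, alpha 0.05, power 0.80, 20% dropout (section 2.2).
- FIQR test-retest r = 0.84 (section 2.5.1).
- Attendance of at least 75%, change scores, Benjamini–Hochberg (section 2.6).

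**Assumed**

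- The number of attenders: 64 (80 × 0.80) or 48 (64 × 0.75).
- Severity is baseline FIQR, or a proxy correlated 0.6 with it.
- As an alternative, a pre–post correlation of 0.70, since r may be lower over months than on short retest.

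**The plan's own figure.** A two-sided two-sample t-test with d = 0.50 needs 63.77, so 64 per arm; 64/0.80 = 80. The sample size reproduces. It is set for a main effect, not an interaction.

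**Correlation produced with no moderation.** Let baseline be x with SD 1, and post = r·x + √(1−r²)·e − 0.5 for every treated patient. With D = post − x:

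- cov(x, D) = r − 1 and var(D) = 2(1−r)
- corr(x, D) = −√((1−r)/2)
- r = 0.84: −√0.08 = −0.283; r = 0.70: −√0.15 = −0.387
- for a proxy correlated 0.6, multiply by 0.6: −0.170 and −0.232

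The constant benefit of 0.5 drops out. The correlation comes only from retest.

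**How often this is declared significant.** Fisher's z at r = 0.84 and n = 64: atanh(0.283) × √61 = 0.291 × 7.81 = 2.27, and Φ(2.27 − 1.96) = 62%. At n = 48: 0.291 × √45 = 1.95, and Φ(1.95 − 1.96) = 50%. Simulation agrees. The Benjamini–Hochberg columns assume three moderators, the other two being null.

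| Severity measure | r | p<0.05, n = 64 | p<0.05, n = 48 | BH, n = 64 | BH, n = 48 |
|---|---|---|---|---|---|
| Baseline FIQR | 0.84 | 63% | 50% | 46% | 34% |
| Baseline FIQR | 0.70 | 90% | 79% | 80% | 64% |
| Proxy, 0.6 | 0.84 | 26% | 21% | 15% | 11% |
| Proxy, 0.6 | 0.70 | 46% | 36% | 29% | 22% |

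Simulation runs differ by about a point; for the proxy at r = 0.84 and n = 64, Fisher's z gives 27%.

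**With TAU in the model.** Regression to the mean is the same in both arms and cancels in the arm × severity term. With 64 TAU patients added, that interaction rejects in about 5% of trials in every row.

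**Age and years from diagnosis.** Regression to the mean in FIQR is not the mechanism here. If such a factor correlated 0.2–0.3 with change in both arms (assumed; the protocol gives no figure), the single-arm path would reject in about 36–69% of trials at n = 64, and a two-arm interaction in about 5%.

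**The case against.** The best reply is that the single-arm model is inferred. The sentence speaks of the effect of NAT-FM, which in a two-arm trial is a contrast with TAU, and the per-protocol label could mean attenders against TAU. Where the authors want one arm only, as with the intrasession EMA, they say so. This stands in part: a model with TAU is not expressly excluded, and with an arm × factor term the false positives computed above would largely go. But the sentence that fixes the data names only treatment patients, by a criterion TAU patients cannot meet, whereas the primary analysis, the NNT and the intersession EMA each name both groups. A model of attenders against TAU would also select one arm on behaviour after randomisation.

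A second reply is that interaction terms and the definition of severity belong in a fuller document, and that the model follows a cited trial. Silence on those details alone would be no finding. The point rests on what the article does fix: the analysis set and the change-score scale.

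A third is that the change-score wording suits mediators better than fixed factors such as age. That is fair for the predictors. The outcome change scores and the attendance restriction are still written for the combined mediation and moderation step.

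A reader might infer that baseline severity will usually look like a moderator. The documents do not support that. Severity is undefined, and at r = 0.84 the plan's own Benjamini–Hochberg step brings the rate below one half. Rates well above one half need severity to be baseline FIQR and an assumed lower r. Benjamini–Hochberg does not cure the fault, though, because it controls error for the wrong null.

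**Conclusion.** The point holds on the natural reading of section 2.6: objective (c) asks about moderation of efficacy relative to TAU, and the analysis described cannot answer it. False declaration of severity as a moderator would be frequent, though not certain. At r = 0.84 it is about 50–63% unadjusted and 34–46% after Benjamini–Hochberg if severity is baseline FIQR, and about 21–26% and 11–15% for a proxy correlated 0.6. The rates are higher at an assumed r = 0.70.

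These figures rest on the assumed meaning of severity, 48–64 attenders, equal pre and post variances and three moderators. For age and years from diagnosis the fault is prognosis mistaken for moderation, and its size depends on an unknown prognostic correlation. The consequence is confined to a third objective whose factors are only said to be possible moderators. The plan should still be changed, since the remedy is cheap.

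**What to change.** In section 2.6:

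1. Separate moderation from mediation.
2. Define severity as a named baseline measure, and use only baseline values as moderators.
3. Test each baseline factor as a group × factor interaction on FIQR at post, +6 and +9 months, in all randomised patients of both arms. Include the factor's main effect and baseline FIQR as covariates (these coincide if severity is baseline FIQR).
4. Label these tests exploratory, because the sample size was not set for interactions.
5. Keep any analysis within NAT-FM attenders as descriptive, and call its associations prognostic only.

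The cost is wording. Table 3 already schedules FIQR and the baseline measures, and section 2.5.1 applies the structural assessment to both arms. The downside is lower power than a within-arm association, so fewer moderators will be declared.
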